## Abstract

**Background:**

The Lifestyle-Integrated Functional Exercise (LiFE) program is effective in improving strength, balance, and physical activity (PA) while simultaneously reducing falls in older people by incorporating exercise activities in recurring daily tasks. However, implementing the original LiFE program includes substantial resource requirements. Therefore, as part of the LiFE-is-LiFE project, a group format (gLiFE) of the LiFE program has been developed, which will be tested regarding its noninferiority to the individually delivered LiFE in terms of PA-adjusted fall incidence and overall cost-effectiveness.

**Methods:**

In a multi-centre, single-blinded noninferiority trial, an envisaged sample of *N* = 300 participants (> 70 years; faller and/or confirmed falls risk; community-dwelling) will be randomized in either LiFE or gLiFE. Both groups will undergo the same strength and balance activities as well as PA promotion activities and habitualization strategies as described in the LiFE programme, however, based on different approaches of delivery: During the 6-month intervention phase, LiFE participants will receive seven home visits and two telephone calls; in gLiFE, the program will be delivered in seven group sessions and also two telephone calls. Main outcomes are a) fall incidence per PA and b) incremental cost-effectiveness ratio comparing costs and quality-adjusted life years between the two interventions. Secondary outcomes include PA behaviour, motor performance, health status, psychosocial status, program evaluation, and adherence. Measurements will be conducted at baseline, 6-month and 12-month follow-up; evaluation of intervention sessions and assessment of psychosocial variables related to execution and habitualization of LiFE activities will be made during the intervention period as well.

**Discussion:**

Compared to LiFE, we expect gLiFE to (a) reduce falls per PA by a similar rate; (b) be more cost-effective; (c) comparably enhance physical performance in terms of strength and balance as well as PA. By investigating the economic and societal benefit, this study will be of high practical relevance as noninferiority of gLiFE would facilitate large-scale implementation due to lower resource usage. This would result in better reach and increased accessibility, which is important for subjects with a history of falls and/or being at risk of falls.

**Trial registration:**

ClinicalTrials.gov NCT03462654. Registered on March 12, 2018.

## Background

Being already high in many Western societies, the proportion of older people—and with it, fiscal and political challenges with respect to health care and society—is projected to increase globally [1]. About a third of older people aged 65 or older experience a fall within 1 year [2, 3], and resulting injuries inevitably have significant repercussions on individuals, the health care system, and the community [4]. Falls are among the top five of the leading health conditions associated with disability in populations aged 60 years and older [5]. Due to this strong impact on individuals, research on falls and fall-related outcomes has received intensified attention in the past decades, and still remains in the spotlight of health-related research. Although many risk factors for falling have been identified in previous research, strength, balance, and gait impairments are among the strongest [6], indicating that respective exercise may be effective in reducing risk and rate of falling. Results of meta-analyses suggest exercise to be the best univariate approach to prevent falls at a population level, however, this depends on the exercise component applied [4, 6]. Sherrington and colleagues recommended balance training as the exercise of choice, ideally accompanied by strength training [4]. Adherence to respective exercise recommendations [7] was reported by only 21.0% of retired seniors, with only 5.3% adhering to both forms of exercise [4, 8]. Several structured training programs which aim to enhance balance and muscle strength (e.g., the Otago Exercise Program [9]) are available [4, 10–15]. While such strength and balance exercise programs have been found effective in intervention studies, they often fail to induce long-term change, adherence (> 6 months), and participation [16, 17]. Another, more general factor often brought into play is physical activity (PA). While its numerous health benefits are well established [18], and some of these are connected to a lower risk of falling [19], findings on the relation between PA and risk of falling remain controversial [20–23]. This might be due to increased fall risk exposure, that is, occurrence of situations associated with falls. As up to one half of falls in the 65+ age group occurs while walking [24, 25], walking duration may be an adequate surrogate for risk exposure time [26]. Despite the large number of older adults not meeting evidence-based PA guidelines [27], and given the popularity of walking activities in older cohorts, such recommendations for regular PA may have to be followed with caution when it comes to the adoption and promotion of PA in subjects with moderate to high fall risk. It may not be sufficient to simply adopt a more active lifestyle; the physical and functional foundation should be established for a “safe gain” in physically active behaviour.

Novel concepts and formats with the potential for large-scale implementation and long-term adherence to strength and balance exercising are urgently needed. With the ‘Lifestyle-integrated Functional Exercise’ (LiFE) program [28], Clemson and colleagues presented a novel approach to prevent falls by improving strength and balance while simultaneously promoting the adoption of a physically more active lifestyle in persons aged 70 years and older. The integration of the LiFE activities is assumed as a gateway behaviour to more PA, meaning that through practicing the functional balance and strength exercises, PA behaviour is enhanced. Unlike structured exercise programs, LiFE promotes the idea to incorporate balance and strength activities into everyday tasks rather than participating in a structured exercise program at certain occasions. In a randomised controlled trial, LiFE was found superior to a structured group exercise and a control program in improving physical function, reducing functional disability, promoting adherence, and enhancing PA while significantly reducing falls [29]. Notwithstanding its effectiveness, implementing LiFE as a home-based program poses high financial requirements and human resources. Program delivery requires seven individual home visits and two follow-up phone calls, in which participants are taught in a one-to-one training how to successfully implement LiFE activities into their personal daily routine. Very recent findings suggest that LiFE may be as effective when delivered in a group setting as compared to the individual approach [30]. Still, an evaluation of a LiFE group format based on a larger sample is missing and warranted [30]. Therefore, as part of the LiFE-is-LiFE project, the original, individually delivered LiFE program was adapted into a group format (gLiFE) with the aim to facilitate large-scale implementation and thus less resource usage. The adapted approach delivered in the trial at hand (gLiFE) was tested in a small pilot study (study registration ID: NCT03412123; concept paper under preparation). In this current LiFE-is-LiFE project, gLiFE is going to be tested for its noninferiority compared to LiFE in terms of fall incidence and cost-effectiveness.

### Aims

We hypothesize in this multi-centre, two armed, single-blinded, randomised noninferiority trial that: *(1)* gLiFE won’t be less efficacious than LiFE in terms of reducing fall incidence expressed as number of falls per PA, i.e., energy expenditure; gLiFE won’t result in a lower intervention retention rate (i.e., percentage of the sample completing the 6-month and 12-month follow-up assessment) as compared to LiFE; *(2)* delivering gLiFE will be cost-effective and less costly compared with LiFE; *(3)* in both groups, physical performance in terms of strength and balance as well as physical activity will be enhanced at comparable levels.

A process evaluation according to guidelines of the Medical Research Council (MRC) for complex interventions [31] will be performed in order to assess quality of implementation and to identify causal mechanisms as well as contextual factors which may affect study outcomes.

## Methods/design

### Study design and setting

This multi-centre, single-blinded noninferiority trial is designed in accordance with the extended CONSORT statement for reporting on noninferiority trials [32]. *N* = 300 participants living in the respective communities are going to be recruited from two study sites (*n* = 150 at each site): The Network Aging Research (Heidelberg, Germany) and the Robert Bosch Hospital (Stuttgart, Germany). This protocol was drafted following the SPIRIT guidelines for randomized trials [33].

### Eligibility criteria

German-speaking, community-dwelling seniors aged 70 years and older being able to walk at least 200 m with or without walking aid will be eligible for participation if they either a) experienced at least one injurious fall within the past year, or b) experienced more than one non-injurious fall within the past year, or c) stated having perceived a balance decline within the past year and needed ≥12 s for the “Timed Up-and-Go” [34] test. In- and exclusion criteria are presented in Table 1; they were chosen in accordance with those defined in the randomised trial by Clemson et al. [29] to ensure external validity of the trial.

**Table 1 Tab1:** Overview of eligibility criteria

Inclusion criteria	Exclusion criteria
- Age: ≥ 70 years	- Exercise > 1/week in past 3 months - Moderate to vigorous physical activity > 150 min/week in past 3 months
- Living at home *OR* “supervised living” without having active assistance	- Medical conditions: - Heart failure (NYHA class III & IV) - Recent cerebrovascular accident (< 6 months) - Parkinson’s disease - On active cancer treatment (last 6 months) - Chronic Obstructive Pulmonary Disease Gold class III & IV - Unstable lower limb fracture - Amputated lower extremity (−ies) - Acute treatment of depression - Uncontrolled resting blood pressures of a systolic > 160 or diastolic > 100 or higher
- Fall risk, defined as > 2 falls within the last 12 months *OR* 1 injurious fall within the last 12 months *OR* subjectively perceived balance decline AND Timed Up-and-Go time ≥ 12 s	
- Able to speak and read in German	
- Able to ambulate 200 m without personal assistance	- Unavailability for home visits within 11 weeks after baseline assessment
	- Travel > 2 months planned within first 6 months of the study
	- Moderate to severe cognitive impairment (Montreal Cognitive Assessment < 23)
	- Current participation in another scientific trial

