### Outcomes

A complete list of screening and outcome parameters and descriptive variables is provided in Table 4. Data include socio-demographics, medical and medication information, neuropsychological status, motor function, health status and economics, physical activity status, psychosocial data, and information on adherence to LiFE activities and group evaluation. To ensure highest possible standardisation of assessments, instructors attended a two-day workshop covering all aspects of screening and assessments.

**Table 4 Tab4:** Overview of descriptive variables and assessment measures over the course of the study

		TS	IS	BA	Int	FU6	FU12
	Socio-demography						
	Age; birthday; gender; living conditions (institutionalised vs. community-dwelling)	x					
	Living alone or not; marital status; school-leaving qualification; years of education; academic grades; retirement age		x				
	German-speaking	x					
	Medical and medication information						
	Height; weight		x			x	x
	Blood pressure^f^		x				
	Vision impairment: *Are you able to read a newspaper or book, with or without visual aid?*	x					
	Hearing impairment (whisper test)		x				
	Fall history and fall-related injuries in the past 12 months	x					
P	Fall calendar^d^ [43]						
	Prevalence of neurologic, pulmonary or cardiac disease	x					
	Comorbidities incl. Treatment; cardiac issues or stroke in past 6 months; pain while walking and resting; blood pressure [mmHg]; pulse [1/min]; use of sedatives or anticonvulsants; number of hospital admissions in past 12 months; urinary incontinence in past 12 months		x				
	Medication use (type, dosage, frequency)			x		x	x
	Neuropsychological status						
	Depressive symptoms: Center for Epidemiologic Studies Depression Scale, 10 item Version [CES-D 10] [80]		x				
	Cognitive status: Montreal Cognitive Assessment [MoCa] [81]		x				
S	Fear of falling: Short Falls Efficacy Scale International [Short FES-I] [53]			x		x	x
	Motor function						
	Occurrence of dizziness or gait insecurity in past 12 months		x				
S	Balance self-efficacy: Activities-specific Balance Confidence Scale [ABC-Scale] [58]			x		x	x
S	Functional mobility: (instrumented) Timed Up-and-Go Test [34]	x		x		x	x
S	Functional capacity: Late-Life Function and Disability Instrument [LLFDI] [57]			x		x	x
S	Static balance: 8 Level Balance Scale [29]			x		x	x
S	Static balance: (instrumented) Modified Clinical Test of Sensory Interaction on Balance [54]			x		x	x

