### Allocation and blinding

After completion of baseline assessments, participants will be randomised in either gLiFE or LiFE by the study coordinators in computer-generated blocks of variable size. To facilitate the gLiFE organisation process, all participants will be asked during the inhouse screening at which weekdays they have time to participate in a morning session (9.30 AM to 11.30 AM) or afternoon session (2.00 PM to 4.00 PM). gLiFE groups will be started once at least 8 and up to 12 persons are randomly allocated to this arm of the intervention and have a match in their schedule. LiFE participants can start the intervention immediately after the 9-day PA recording period has ended. All research staff will be eligible to perform telephone screenings, inhouse screenings, and baseline assessments prior to randomisation. Follow-up assessments after randomization will be performed by assessors blinded towards group allocation. To ensure blinding of assessors, the database used in this study will only show information not related to the intervention when assessors are logged in. For trainers and study coordinating staff, all information will be unlocked. Outcome measures which identify group allocation such as evaluation of intervention sessions will be collected by unblinded research staff.

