### Statistical analyses

Statistical analyses will follow the ICH Harmonized Tripartite Guideline “Statistical Principles for Clinical Trials” E9 [64]. Based on the trial of Clemson et al., we expect a decrease in fall incidence (expressed as falls per amount of PA) of 79.4% for LiFE [29]. A one-sided Pearson’s chi-square test will be used to test noninferiority with α = 0.05 in the fall incidence between LiFE and gLiFE with a noninferiority margin of − 15.9%.

All main analyses will be done according to the intention-to-treat principle, which will include all randomized participants in the analysis dataset for whom a baseline assessment was conducted, regardless of their adherence to and compliance with the assigned treatment. Participants who withdrew or dropped out are requested to participate in follow-up assessments; those who are lost to follow-up will be included in the full analysis set by imputing their missing data. Secondary analyses will provide a more detailed insight on which dimensions both treatments are effective to deepen the understanding of trial results. Understanding the underlying physiological pathways in both formats will increase knowledge on the effectiveness of the intervention components and strategies and thereby improve the design and implementation of both LiFE treatments. Additionally, sensitivity analyses will be performed to explore the effect of missing values and attrition during treatment:Per-protocol analysis of the dataset restricted to all participants with available measurements for the primary variables and no protocol violations.If the number of missing values is substantial (higher than 5% for a given variable), a sensitivity analyses will be conducted for imputing missing values.

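### The primary noninferiority test is fixed as an unadjusted two-group chi-square, although the sample mixes past-year fallers with people who need no fall and fall history is recorded before randomisation

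*Protocol article*

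**What the plan says.** Under Eligibility criteria, a person may enter in one of three ways: having "experienced at least one injurious fall within the past year"; having "experienced more than one non-injurious fall within the past year"; or, with no fall required, having "stated having perceived a balance decline within the past year and needed ≥12 s for the “Timed Up-and-Go" test.

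Table 4 (Outcomes) lists "Fall history and fall-related injuries in the past 12 months" as a telephone-screening item, so it is known before allocation.

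Statistical analyses gives the reference value: "we expect a decrease in fall incidence (expressed as falls per amount of PA) of 79.4% for LiFE". It then names the primary test: "A one-sided Pearson’s chi-square test will be used to test noninferiority with α = 0.05 in the fall incidence between LiFE and gLiFE", with a margin of 15.9%. Sample size derives that margin as 20% of the original trial's reduction. It states 81 per group, or 108 after 25% drop-out; the planned total is 300, with 150 per arm. The primary analysis as stated includes no covariate.

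**The concern.** The primary outcome is future falls relative to energy expenditure. People who have fallen in the past year and people admitted on balance decline plus a slow mobility test may well differ on it. If so, the faller share will differ somewhat between arms by chance, and an unadjusted comparison carries that difference into the estimate.

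The Discussion says that gLiFE will be recommended if it is within the margin, so one verdict carries the recommendation. Adjustment chosen after an imbalance has been seen would be open to challenge. Adjustment fixed beforehand would not.

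**Working it through.** **1. The plan's own figure.** Inputs: reference proportion 0.794, margin 0.2 × 0.794 = 0.1588, one-sided α 0.05. Power is not stated, so 80% is assumed.

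n = (1.645 + 0.842)² × 2 × 0.794 × 0.206 / 0.1588² = 80.2, rounded up to 81 per group. This matches. Drop-out: 81 / 0.75 = 108, which also matches. The formula treats 79.4% as a simple proportion and has no term for a covariate or stratum.

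**2. Power at the planned size.** 150 × 0.75 gives about 112 evaluable per arm. SE = √(2 × 0.794 × 0.206 / 112) = 0.0540. Power = Φ(0.1588 / 0.0540 − 1.645) ≈ 0.90.

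**3. Chance imbalance in faller share.** Assumed, not in the documents: a share s of 30-70% with a past-year fall, and a success proportion 10, 20 or 30 points lower in fallers, with the overall mean held at 0.794. (A 70% share with a 30-point gap is impossible, because it needs a proportion of 1.004 in non-fallers.)

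SD of the between-arm difference in share = √(2s(1 − s) / 112) = 0.061 at s = 0.3 or 0.7, and 0.067 at s = 0.5. The 95% limit is 1.96 × SD = 12.0 to 13.1 points. Multiplying by the gap gives the shift in the estimated difference.

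| Gap (points) | Shift at 95% limit (points) | Share of 15.88-point margin | Power, arms truly equal, imbalance against gLiFE | False noninferiority, true difference at margin, imbalance favouring gLiFE |
|---|---|---|---|---|
| 10 | 1.2-1.3 | 8% | 0.86 | 0.08 |
| 20 | 2.4-2.6 | 15-16% | 0.80-0.81 | 0.11-0.12 |
| 30 | 3.6-3.9 | 23-25% | 0.73-0.75 | 0.15-0.16 |

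With no imbalance, the last two columns read 0.90-0.92 and 0.04-0.05. Both are conditional on an imbalance at the 95% limit. They are not average error rates.

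**4. Averaged over all randomisations.** Trials were simulated at 112 per arm, 200,000 per scenario, comparing a crude difference with one stratified on fall history using Mantel-Haenszel weights. Site was not simulated.

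- Type I error: crude 0.049-0.050; stratified 0.051-0.052.
- Power with equal arms: crude 0.903; stratified 0.907 (s = 0.5, gap 10) to 0.936 (s = 0.5, gap 30), a gain of about 0.4 to 3 points.
- The two verdicts differ in about 2-5% of trials with equal arms.

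**5. Variance.** The proportional reduction from adjustment is s(1 − s) × gap² / (0.794 × 0.206). At s = 0.5 and gap 0.30 this is 0.0225 / 0.1636 = 14%; at s = 0.3 and gap 0.10 it is 0.0021 / 0.1636 = 1.3%. This is the imbalance of step 3 seen on average, so the two must not be added together.

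**The case against.** The strongest reply is that an unadjusted comparison of randomised arms is valid. Its error rate already allows for chance imbalance, and step 4 confirms this. That stands: the point is about precision and about how one trial reads, not about bias. A reader who inferred that the noninferiority conclusion is unsound would be going further than the calculations allow.

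Three other stronger readings are not supported.

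- *The randomisation is unstratified.* Allocation and blinding says only that "participants will be randomised in either gLiFE or LiFE by the study coordinators in computer-generated blocks of variable size". Silence on strata in a condensed article does not show that there are none, and the point does not depend on it.
- *The imbalance uses up much of a 20% margin.* A relative shift in fall rate cannot be set beside that 20%. The margin is 20% of 79.4%, or 15.9 percentage points. Even if 79.4% is read as a rate reduction, the boundary is 63.5%, a rate ratio of 0.365 / 0.206 = 1.77, not 1.20.
- *Entry route is the natural covariate.* The routes overlap: a faller may also meet the balance route, and someone entering by balance decline may have had a single non-injurious fall. The text asks for more than one non-injurious fall where Table 1 asks for more than two falls.

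It is also fair to say that the documents give no prognostic gap on the actual outcome. If slower people are also less active, their smaller energy expenditure would raise falls per activity and could narrow the gap.

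An unseen analysis plan might contain adjusted models. But the article does not leave the primary test open, so an adjusted primary analysis there would depart from the published one.

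**Conclusion.** The point holds as a matter of efficiency and of robustness in a single trial. The stated primary test cannot use a plausible predictor that is recorded before randomisation.

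Under the assumptions in step 3, an imbalance at the 95% limit moves the estimate by about 1-4 points, or 8-25% of the margin, and adjustment adds about 0.4-3 points of power. Overall type I error is about 0.05 either way. If every randomised participant counts, as the planned intention-to-treat analysis with imputation intends, the largest 95% limit falls from 13.1 to 1.96 × √(0.5 / 150) = 11.3 points, so the effect is somewhat smaller.

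The size rests wholly on the assumed share and gap. The case for the change is that it costs almost nothing, not that the harm is large.

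**What to change.** In Statistical analyses, state that the primary between-arm comparison is adjusted for recorded past-year fall history (number of falls, or any versus none) and for site. Name a method that permits it:

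- if the proportion scale is kept, a Mantel-Haenszel weighted difference over fall-history and site strata, tested against the 15.9-point margin;
- if the outcome is analysed as defined under Primary outcome measures, a count regression with energy expenditure as exposure. The margin must then be stated on the rate-ratio scale.

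Keep the unadjusted comparison as a supporting analysis.

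Use recorded fall history and not entry route. If entry route is used at all, the fall criterion in the Eligibility criteria text and the one in Table 1 must first be reconciled.

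The cost is a few lines of wording, fixed before group outcomes are seen. Fall history and site are already held for the 127 participants enrolled at submission, so the change covers them too and needs no new data collection or allocation list.
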